### 8.2 Definition of solicited adverse events

Within this study protocol solicited adverse events are defined as all events recorded by the subjects in the diary provided to them following every vaccination. For each of the 7 days post-vaccination the subjects are requested to monitor and record local symptoms, i.e. erythema, swelling and pain at the site of injection as well as systemic symptoms, i.e. body temperature, headache, chills, myalgia, nausea and fatigue.

### 8.3 Definition of unsolicited adverse events

At every study visit the Investigator should ask the subject if they have experienced any adverse events since their last visit. All intercurrent diseases reported by the subject, regardless of whether recorded in the subject diary or not, need to be recorded by the Investigator in the appropriate page of the case report form.

The intensity and causality of the events will be graded according to the procedures described under 7.1.7 and 7.1.8 respectively.

### 8.4 Definition of “adverse event of special interest”

An “adverse event of special interest” is defined in this study as an adverse event fulfilling any of the following features:

- Any cardiac symptom
- ECG changes, which are determined to be clinically significant
- Cardiac enzymes elevated above ULN

Adverse events of special interest are to be reported according to the procedures and timelines applicable for serious adverse events.

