**All study subjects:**

3. Male and female subjects between 18 and 40 years of age without history of smallpox vaccination.
4. Women must have a negative serum pregnancy test at screening and a negative urine pregnancy test within 24 hours prior to vaccination.
5. Women of childbearing potential must have used an acceptable method of contraception for 30 days prior to the first vaccination, must agree to use an acceptable method of contraception during the study, and must not become pregnant for at least 28 days after the last vaccination. A woman is considered of childbearing potential unless post-menopausal or surgically sterilized. (Acceptable contraception methods are restricted to abstinence, barrier contraceptives, intrauterine contraceptive devices or licensed hormonal products.)
6. Read, signed and dated informed consent document after being advised of the risks and benefits of the study in a language understood by the subject signed, and prior to performance of any study specific procedure.
7. Troponin I < 2 fold ULN.

8. White blood cells  $\geq 2500/\text{mm}^3$  and  $< 11,000/\text{mm}^3$ .
9. Absolute neutrophil count (ANC) within normal limits
10. Negative urine glucose by dipstick or urinalysis.
11. Hemoglobin within normal limits.
12. Platelets within normal limits.
13. Adequate renal function defined as:
  - a. Serum creatinine without clinically significant findings
  - b. Urine protein  $< 30 \text{ mg/dL}$  or none or trace proteinuria (by urinalysis or dip stick).
14. Adequate hepatic function defined as:
  - a. Total bilirubin  $\leq 1.5 \times \text{ULN}$  in the absence of other evidence of significant liver disease
  - b. AST (SGOT), ALT (SGPT) and alkaline phosphatase without clinically significant findings
15. Electrocardiogram (ECG) without clinically significant findings (e.g. any kind of atrioventricular or intraventricular conditions or blocks such as complete left or right bundle branch block, AV-node block, QTc or PR prolongation, premature atrial contractions or other atrial arrhythmia, sustained ventricular arrhythmia, 2 premature ventricular contractions (PVC) in a row, ST elevation consistent with ischemia).
16. Availability for follow-up for the planned duration of the study (26 weeks after last vaccination).

---

Exclusion  
criteria

1. Pregnant or breast-feeding women.
2. Uncontrolled serious infection i.e. not responding to antimicrobial therapy.

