## 4.2 Inclusion criteria

### Group 1:

1. Subjects without present or history of any kind of atopy. Subjects with seasonal allergies can only be enrolled if an association with other atopic disorders such as allergic rhinitis and asthma can be excluded.

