### **7.1.4 ECG assessments**

A standard 12-lead ECG will be taken on all subjects at screening (Visit SCR) and 7 - 14 days after each vaccination (for Visit 2: 7-10 days and Visit 4: V3+10-14 days). For Visit 5 and the follow-up visit, an ECG is only done if clinically indicated.

ECGs will be evaluated by a centralized procedure. Unclear ECG abnormalities will additionally be evaluated by a central Cardiologist. The workflow / communication flow will be provided in a separate manual.

If clinically indicated, or in case of any kind of cardiac symptoms such as but not limited to chest pain, dyspnoea, arrhythmia, or edema subjects will be referred for a cardiac evaluation by a Cardiologist and further diagnostic tests will be done as recommended by this Cardiologist (e.g. (treadmill) ECG, cardiac enzymes, echocardiogram). Subjects will then be followed up for at least one year in a frequency determined by the Cardiologist.

Such adverse events fulfill the definition of an “adverse event of special interest” and are to be handled respectively reported as described under section 8.4.

Using replication-competent vaccinia-based smallpox vaccines during smallpox vaccination programs in the US during the last years, cases of acute myocarditis and pericarditis were observed (Grabenstein and Winkenwerder, 2003).

Case definitions as published by the US Center of Disease Control (CDC) ("Update: Cardiac-Related Events During the Civilian Smallpox Vaccination Program --- United States, MMWR May 30, 2003, Vol. 52, No. 21, p. 494") are provided in Appendix II in order to:

- help Investigators to recognize possible events of acute myocarditis and/or pericarditis and
- distinguish from unspecific and isolated ECG changes without or with unclear clinical meaning

Subjects who develop any kind of cardiac symptoms during the study such as but not limited to chest pain, dyspnea, arrhythmia, or edema are referred to a Cardiologist for cardiac evaluation including (treadmill) ECG, cardiac enzymes and echocardiogram. Depending on the results of this evaluation further diagnostic tests will be done as recommended by the Cardiologist and patients will be followed up for at least one year in a frequency determined by the Cardiologist. Furthermore unclear ECG abnormalities observed during the study will be examined upon recommendation of the cardiologist.

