#### Unsolicited adverse events:

Unsolicited adverse events will be coded with the MedDRA coding terminology. The intensity of adverse events will be graded according to section 7.1.7.

The number of adverse events and number of patients with at least one adverse event for each preferred term will be descriptively compared between treatment groups.

The occurrence of any grade 3 or higher adverse reaction probably, possibly or definitely related to the study vaccine within 28 days after vaccination will be compared between treatment groups.

The occurrence, relationship and intensity of *adverse events of special interest* at any time during the study will be separately listed and tabulated. The incidence of such AEs will be compared between treatment groups by means of the exact test of Fisher (or its normal approximation, the chi-squared test).

*Serious adverse events* will be listed separately. Each SAE will be described individually in detail. The number of subjects with at least one SAE will be compared between treatment groups by means of the exact test of Fisher (or its normal approximation, the chi-squared test).

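### The Fisher comparison of special-interest events counts dyspnoea of any origin between an atopy-free group and an atopic one, so it can show an excess in atopic dermatitis unrelated to the vaccine; separately, the troponin rules disagree and add noise

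*Protocol*

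**What the plan says.** **What is counted.** Protocol 8.4 defines an adverse event of special interest by three features: "Any cardiac symptom", clinically significant ECG changes, and "Cardiac enzymes elevated above ULN". The symptom feature carries no condition on cardiac origin, and the enzyme feature makes no reference to the subject's own baseline. Section 7.1.4 describes the symptoms as "any kind of cardiac symptoms such as but not limited to chest pain, dyspnoea, arrhythmia, or edema" and adds "Such adverse events fulfill the definition of an" adverse event of special interest.

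**Who is compared.** In 4.2, Group 1 consists of "Subjects without present or history of any kind of atopy". Seasonal allergy is admitted there only if a link with allergic rhinitis or asthma is ruled out. Group 2 has no matching bar. For lung disease, exclusion 7 in 4.3 removes only severe, clinically significant disorders. Section 6.4 vaccinates both groups.

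**How they are compared.** Section 9.4.3: "The incidence of such AEs will be compared between treatment groups by means of the exact test of Fisher", with the chi-squared test as the alternative. Occurrence, relationship and intensity are also listed and tabulated.

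**Troponin.** Four places set a threshold:
- Inclusion criterion 7, for all subjects: "Troponin I < 2 fold ULN".
- 8.4: any value above ULN.
- 8.1: a laboratory value is an adverse event if the investigator finds it clinically significant or if it reaches Grade 3. Appendix I puts troponin Grade 3 at 5 x ULN or more, and values between ULN and 2 x ULN at Grade 1.
- 7.1.9, footnote: any abnormality in a scheduled troponin enters the cardiac algorithm.

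**The concern.** The test is meant to show whether cardiac events are more frequent in AD. Dyspnoea has a common non-cardiac source in asthma, and the entry criteria remove that source from one of the two compared groups only. Since both groups receive the vaccine, a difference in all-cause incidence cannot separate atopic background from a vaccine effect.

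A narrower standard exists in Appendix II, where a possible myocarditis needs symptoms judged probably cardiac and no other likely explanation. Section 7.1.4 uses it only to help investigators recognise cases; the compared count does not use it.

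The troponin rules raise a different question. A value of 1.5 x ULN at Visit 2 or 4, unchanged from screening, is acceptable at entry, above the 8.4 threshold, Grade 1 in Appendix I and an abnormality for 7.1.9. Sites could classify identical values differently.

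At stake is the reading of cardiac safety in AD, which feeds a potential EUA package (9.4, Appendix IV). The primary ELISA conclusion is not affected.

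**Working it through.** **Inputs.** 230 healthy and 330 AD subjects (Appendix V table). Assumed, because the protocol does not state them: two-sided 5% for the Fisher test, and the background rates below.

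**1. The protocol's own safety figure.** Appendix IV gives 298 subjects to detect one reaction of incidence 1:100 with 95% certainty. Check: 1 − 0.99^298 = 0.94996 and 1 − 0.99^299 = 0.95046. The exact answer is 299, so 298 reproduces to within one subject. That sizing presumes no background incidence. No sizing is given for the special-interest comparison, where background is the issue.

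**2. Counts that reach significance.** Two-sided Fisher exact, healthy of 230 versus AD of 330:

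| Healthy | AD | p |
|---|---|---|
| 0 | 4 | 0.15 |
| 0 | 7 | 0.045 |
| 1 | 7 | 0.15 |
| 2 | 7 | 0.32 |
| 2 | 13 | 0.032 |
| 5 | 20 | 0.036 |

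Seven against none is just enough, and a single healthy-group event undoes it.

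**3. Chance of a significant AD excess with no vaccine effect.** With p1 and p2 the background rates in healthy and AD subjects, sum Bin(i; 230, p1) × Bin(j; 330, p2) over all pairs (i, j) for which Fisher p ≤ 0.05 and j/330 > i/230:

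| Healthy rate | AD equal | AD +1 point | AD +2 points | AD +3 points |
|---|---|---|---|---|
| 1% | 0.5% | 8% | 29% | 56% |
| 2% | 1.4% | 8% | 23% | 42% |
| 5% | 1.9% | 6% | 14% | 26% |

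One, two or three points among 330 subjects are 3.3, 6.6 or 9.9 extra expected events. At equal rates from 0.5% to 8% the probability runs from 0.05% to 2.1%, below the nominal 2.5% per side.

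**4. Troponin as equal background.** The entry limit is the same in both groups, so take a true difference of 1% versus 4% and add the same amount to each:

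| Added to both groups | Chance of detecting the difference |
|---|---|
| none | 56% |
| +1 point | 42% |
| +2 points | 34% |
| +5 points | 23% |

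Equal background dilutes the comparison. It does not shift it towards AD.

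**The case against.** **What a reader might infer, and why it goes too far.**
- *That the troponin overlap produces an AD excess.* The entry limit applies to all subjects, and nothing in the protocol suggests higher troponin in AD. Step 4 shows dilution only.
- *That a stable elevation is always counted.* An event under 8.4 must first be an adverse event. Section 8 treats changes seen before the first vaccination as baseline signs and symptoms, and 8.1 requires clinical significance or Grade 3. These shield stable values in part. What remains is that the sections disagree. The 7.1.9 figure is not available in the text read, so whether it considers baseline is unknown.
- *That oedema adds a second route because SCORAD scores it.* The SCORAD item rates skin lesions on individual areas. A shared word does not make eczema a cardiac symptom.
- *That seven AD events against none should be expected.* About 6.9 events follow from 330 × 21% with asthma × 10% reporting dyspnoea, but neither rate is in the protocol. With 10% × 10% the expectation is 3.3, and 3 versus 0 gives p = 0.27.

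**The remaining defence.** Section 7.1.4 speaks of cardiac symptoms and has the investigator rate the event, so an obviously asthmatic episode need not be counted. Relationship is tabulated. The comparison is secondary, with no stated alpha or decision rule. Disease background affects every all-cause comparison of AD with healthy subjects.

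This limits the harm to misreading. It does not remove the problem: 7.1.4 names dyspnoea and declares such events to fulfil the definition, neither section states a cardiac-origin condition, and a tabulation of relationship does not change the tested count.

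**Conclusion.** The point holds for dyspnoea. The all-cause Fisher comparison can return an AD excess that reflects atopy and not the vaccine. With 1% background in healthy subjects, an AD-only addition of 1 to 3 points makes this happen in about 8% to 56% of trials; with 5% background the range is about 6% to 26%. These figures rest on assumed rates and a two-sided 5% level. They also assume that investigators do count atopic dyspnoea as a special-interest event, which the wording permits but does not force.

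The troponin point holds only as an inconsistency among the entry criteria, 8.1, 8.4 and 7.1.9. It adds noise to both groups and can mask a true difference.

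This should be corrected because the category is cardiac and the AD data are intended for an EUA package. It does not threaten the primary conclusion.

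**What to change.** Leave 8.4 unchanged for reporting, listings and clinical follow-up. In 9.4.3:

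1. Compare the symptom, ECG and enzyme components separately by group.
2. Count troponin in the comparison only when it is above ULN and increased from the subject's own screening value. Show shifts from screening as well, because a trivial rise would otherwise look like a real one.
3. Keep the all-cause Fisher test. Beside it, compare events for which the cardiologist evaluation already required by 7.1.4 found no non-cardiac cause. Tabulate possible, probable and confirmed Appendix II cases by group.
4. Reconcile 8.1, 8.4 and 7.1.9 on when a troponin value is an adverse event.

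**Cost.** Some rewording, a few derived flags and additional tables. Screening and post-vaccination troponin are already measured (7.1.3), and the cardiologist evaluation is already required. The counts in item 3 will be smaller and depend on an attribution made in an open-label trial, which is why the all-cause comparison stays.

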## 8.5 Definition of serious adverse events (SAEs)

A serious adverse event (experience) or reaction is any untoward medical occurrence or effect that at any dose:

1. Results in death,
2. Is life-threatening\*,
3. Requires inpatient hospitalization or prolongation of existing hospitalization,
4. Results in persistent or significant disability or incapacity,
5. Is a congenital anomaly or birth defect,
6. or is an otherwise important medical event.

*\*The term "life-threatening" in the definition of "serious" refers to an event in which the patient was at risk of death at the time of the event; it does not refer to an event which hypothetically might have caused death if it were more severe.*

Medical and scientific judgment should be exercised in deciding whether expedited reporting is appropriate in other situations, such as important medical events that may not be immediately life-threatening or result in death or hospitalization but may jeopardize the patient or may require intervention to prevent one of the other outcomes listed in the definition above. These should also usually be considered serious.

Examples of such events are intensive treatment in an emergency room or at home for allergic bronchospasm; blood dyscrasias or convulsions that do not result in hospitalization; or development of drug dependency or drug abuse.

## 8.6 Reporting of SAEs and adverse events of special interest

All serious adverse events (SAEs) or adverse events of special interest (see definition 8.4) occurring throughout the entire course of the study have to be reported to Kendle Safety Department. The study site has to send by e-mail or fax the completed serious adverse event form to Kendle Safety Department within 24 hours of becoming aware of the adverse event.

Kendle Safety forwards all serious adverse events and adverse events of special interest within 24 hours to Bavarian Nordic Drug Safety. Bavarian Nordic is responsible for expedited reporting to the US regulatory authorities (FDA) in compliance with regulations and to the responsible NIH-DMID representatives. For Mexico, all expedited cases will be forwarded by Bavarian Nordic Drug Safety to Kendle Mexico for submission to the Mexican Ministry of Health with an accompanying cover letter in Spanish.

The flowchart below outlines the reporting process and timelines:

[figure not shown]

\* if at least possibly causally related

Please fax SAE reports to the following number depending upon the country of origin:

### Kendle Safety Mexico:

From sites outside Mexico City,

[contact]  
([contact])

From sites inside Mexico City,

[contact]  
([contact])

The Investigator should not delay reporting because of missing information. Nonetheless, the report should be as complete as possible. This initial notification should include, as a minimum, sufficient information to permit identification of the following:

the reporter  
adverse event(s)  
involved study medication

the subject  
date of onset

## 9. Statistical Considerations

The primary objective of this trial is to compare the two vaccination groups with regard to total antibodies.

### 9.1 Sample size calculation

The sample size calculation is based on the primary immunogenicity endpoint '**MVA-specific seroconversion rate**'.

The primary hypothesis is to show that the humoral immune response of the group with diagnosed atopic dermatitis (Group 2) is not statistically inferior compared to the group with healthy subjects (Group 1) at 10-14 days after the second vaccination (Visit 4). The study should demonstrate that the Group 2 seroconversion rate is not worse than the Group 1 seroconversion rate by more than a pre-specified amount. This amount is called the non-inferiority margin ( $\Delta$ ).

Suppose  $p_1$  is the seroconversion rate in healthy subjects (group 1) and  $p_2$  is the seroconversion rate in the subjects with atopic dermatitis (group 2).

The test on non-inferiority will be applied for the following hypothesis:

$$H_0: p_2 - p_1 \leq -\Delta \quad \text{versus} \quad H_1: p_2 - p_1 > -\Delta, \text{ where}$$

$\Delta$  is the non-inferiority margin and is chosen in this trial as 5%.

From the experience in the pilot trial POX-MVA-007 in subjects with atopic dermatitis subjects, it is anticipated that the seroconversion rate in both groups reaches at least 99%.

The above hypothesis will be tested based on an exact, unconditional test for binomial differences. In addition an exact one-sided 97.5% unconditional confidence interval for the difference of proportions will be calculated. If the lower limit of this confidence interval is greater than  $\tilde{\alpha}$  5% (or equivalent the p-value of the non-inferiority test is less than 5%) then the null hypothesis will be rejected (StatXact®, Chan 1998, Agresti and Min 2001).

Assuming a significance level of 5%, a power of > 80%, expected seroconversion rates of 99% in both groups, this yields to a sample size of 124 per group (248 in total). In order to account for drop outs, a total of 130 subjects per group (260 in total) will be treated.

For the statistical consideration of the protocol extension, please refer to Appendix IV.

### 9.2 Endpoints

#### 9.2.1 Immunogenicity endpoints

Primary endpoint

- ELISA specific seroconversion rate at visit 4
  - *Seroconversion is defined as the appearance of antibody titers  $\geq 1:50$  in a vaccinia specific IgG ELISA for initially seronegative subjects or twofold increase of the antibody titer compared to the pre-existing baseline titer for subjects with a pre-existing antibody titer in the ELISA.*

Secondary endpoints

- ELISA specific seroconversion rate at visits 2, 3, 5 and F-U.
- Geometric mean titers (at all blood sampling time points).
  - *The geometric mean titer (GMT) is calculated by taking the antilogarithm of the mean of the log10 titer transformations. Antibody titers below the cut-off of the assay will be given an arbitrary value of one for the purpose of calculation.*
- Neutralization assay specific seroconversion rates and geometric mean titers (at all blood sampling time points).
  - *Seroconversion is defined as Appearance of antibody titers  $\geq 15$  in a vaccinia specific plaque reduction neutralisation assay for initially seronegative subjects or twofold increase of the antibody titer compared to the pre-existing baseline titer for subjects with a pre-existing antibody titer in the PRNT.*
  - *The GMT is calculated by taking the antilogarithm of the mean of the log10 titer transformations. Antibody titers below the cut-off of the assay will be given an arbitrary value of one for the purpose of calculation.*
- Subgroup of 50 subject samples from Group 1 (healthy) and 110 subject samples from Group 2 (AD) collected at US sites: IFN gamma producing T-cells collected at Visits 1, 2 and 4 in response to stimulation with MVA-BN® (IMVAMUNE®) detected by Enzyme-Linked Immunospot (ELISPOT). The percentage of IFN gamma positive cells in T-cell populations compared to non-stimulated cells will be reported.

The primary time point for data analysis will be 10 – 14 days after the last vaccination (Visit 4) . Other time points at Visit 2, 3, 5 and F-U are used as secondary analysis time points.

### 9.2.2 Safety and reactogenicity endpoints

#### Secondary endpoints

- Occurrence of any grade 3 adverse event probably, possibly or definitely related to the study vaccine within 28 days after vaccination.
- Occurrence, relationship and intensity of any serious adverse event at any time during the study.
- Occurrence of solicited local adverse events (redness, swelling and pain) within 1 week after each vaccination (Days 0-7): Intensity, duration, and relationship to vaccination.
- Occurrence of solicited systemic adverse events (redness, swelling and pain) within 1 week after each vaccination (Days 0-7): Intensity, duration, and relationship to vaccination.
- Occurrence of unsolicited non-serious adverse events within 4 weeks after each vaccination (Days 0-28): Intensity, duration and relationship to vaccination.

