### 3. Study design

#### 3.1 Experimental design

This study is an open-label, controlled, phase II clinical trial to evaluate immunogenicity and safety of MVA-BN® (IMVAMUNE®) smallpox vaccine in 18-40 year old subjects with diagnosed atopic dermatitis.

The following two subject groups are compared:

Group 1: Healthy, vaccinia naïve subjects without atopic disease

Group 2: Vaccinia naïve subjects with diagnosed atopic dermatitis. “Diagnosed” atopic dermatitis includes subjects with either history of or subjects with currently active (defined as SCORAD  $\leq$  30, Kunz et al., 1997) atopic dermatitis.

[figure not shown]

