**VISIT 5 (VISIT 3 + 28-35 DAYS)**

- Targeted physical examination including evaluation of vital signs, especially listening to the heart and lungs
- Brief interview concerning AD status- including SCORAD (Group 2, active AD only)
- ECG (only if clinically indicated)
- Urine pregnancy test (if applicable)
- Safety Lab (only if clinically indicated)
- Blood draw for antibody analysis
- Recording and documentation of AEs

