|                 | the known effects of the study medication or substance class provide no indication of a (concomitant) causal connection with or worsening caused by the study medication and there is another cause which serves as an adequate explanation                                         |
|                 | and/or                                                                                                                                                                                                                                                                       |
|                 | although the known effects of the study medication or substance class make it possible to derive a plausible causal chain with regard to a (concomitant) causal connection or worsening, however, another cause is considerably more likely                                         |
|                 | and/or                                                                                                                                                                                                                                                                       |
|                 | another cause of the AE has been identified and a (concomitant) causal connection with or worsening caused by the study medication is unlikely.                                                                                                                                     |
| Possible | A plausible causal chain with regard to a (concomitant) causal connection with / worsening of the AE can be derived from the pharmacological properties of the study medication or substance class. However, other approximately equally likely causes are known                    |
|                 | or                                                                                                                                                                                                                                                                           |
|                 | although the pharmacological properties of the study medication or substance class provide no indication of a (concomitant) causal connection with / worsening of the AE, there is no other known cause which provides an adequate explanation.                                     |

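### The only graded between-group comparison of unsolicited adverse events counts only events rated as related, by raters who know AD status, so severe skin or AD events can be under-counted in Group 2

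*Protocol*

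**What the plan says.** Protocol section 9.2.2 lists five secondary safety endpoints. The first is "Occurrence of any grade 3 adverse event probably, possibly or definitely related to the study vaccine within 28 days after vaccination". Section 9.4.3, under unsolicited adverse events, states the matching between-group analysis, whose outcome is "The occurrence of any grade 3 or higher adverse reaction probably, possibly or definitely related to the study vaccine within 28 days after vaccination". The endpoint names Grade 3 only, whereas the analysis takes Grade 3 and above. The intensity scale in 7.1.7 has a Grade 4.

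Relatedness comes from routine event recording. Section 8.3 says: "The intensity and causality of the events will be graded according to the procedures described under 7.1.7 and 7.1.8 respectively". Under 7.1.8, one route to 'Unlikely' is a plausible vaccine mechanism where nevertheless "another cause is considerably more likely". 'Possible' has two routes: other causes are known but are about equally likely, or "there is no other known cause which provides an adequate explanation". Only 'Possible' and above enter the endpoint.

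Section 3.1 describes the design: "This study is an open-label, controlled, phase II clinical trial to evaluate immunogenicity and safety of" the vaccine. Both groups receive it. Group 1 must be free of present or past atopy, and Group 2 is defined by AD (section 4.2).

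AD status is also assessed directly. SCORAD is scored at screening in active AD, and Visit 5 includes "Brief interview concerning AD status- including SCORAD (Group 2, active AD only)". Section 9 names no endpoint or analysis for these data.

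**The concern.** Safety in AD subjects compared with healthy subjects is the first secondary objective (section 2). Section 1.5 explains why AD matters: conventional vaccinia vaccines can cause a severe skin complication in these patients. Severe skin events in Group 2 are therefore among those a reader will look for first.

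A relatedness filter is neutral between groups only if raters apply it alike in both. Here one group carries a chronic skin disease that can explain a severe rash, pruritus or skin infection, and the other was selected to have none. An event readily put down to underlying AD in Group 2 may have no competing explanation in Group 1. Any resulting error removes events from Group 2 and makes the groups look more alike. A null result on this comparison would then be hard to interpret, and the protocol states no graded comparison free of the filter to set beside it.

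**Working it through.** **1. Which planned comparisons use grade, and which use the filter (9.4.3)?**

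| Comparison between groups | By grade? | Related events only? |
|---|---|---|
| Solicited local and systemic events | Yes | No |
| Unsolicited events by preferred term | No | No |
| Unsolicited Grade 3 or higher within 28 days | Yes | Yes |
| Adverse events of special interest (incidence) | No | No |
| Serious adverse events (subjects with at least one) | No | No |

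The solicited list (8.2) covers injection-site erythema, swelling and pain, plus temperature, headache, chills, myalgia, nausea and fatigue. It does not reach skin disease away from the injection site. Events of special interest (8.4) are cardiac only. A severe but non-serious AD flare therefore has two stated comparisons: preferred term, which ignores grade, and the third row, which requires a related rating.

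**2. Can the filter act differently by group?** By the wording of 7.1.8, yes. The event is dropped if another cause is considerably more likely, and kept if the other cause is about equally likely or there is none. Underlying AD is available as another cause only in Group 2. The direction is fixed (Group 2 loses events), but the amount is not.

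**3. The protocol's own safety sizing.** Appendix IV states that 298 subjects suffice to detect one reaction of incidence 1:100 with 95% certainty. By the binomial formula P(at least 1) = 1 − (1 − p)^N:
- N = 298: 1 − 0.99^298 = 0.94996
- N = 299: 1 − 0.99^299 = 0.95046

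The stated figure reproduces to within one subject. At N = 300 the probability is 95.1%.

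**4. Effect of under-counting on detection (assumed).** Let f be the share of true Group 2 reactions rated at least 'Possible'. The documents give no value for f. With N = 300 and p = 0.01 × f:

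| f | P(at least 1 counted) |
|---|---|
| 1 | 95.1% |
| 0.75 | 89.5% |
| 0.5 | 77.8% |
| 0.25 | 52.8% |

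**5. Effect on the comparison (assumed).** Group sizes are 230 and 330 (Appendix V). Section 9.4.3 names no test for this comparison; Fisher's exact test, two-sided, is used here because that section names it elsewhere. Suppose 2 of 230 healthy subjects (0.9%) and 20 of 330 AD subjects (6.1%) have a severe event, with misattribution in Group 2 only:

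| Group 2 events rated unrelated | Counted, Group 2 | Counted, Group 1 | Fisher p |
|---|---|---|---|
| None | 20/330 (6.1%) | 2/230 (0.9%) | 0.001 |
| Half | 10/330 (3.0%) | 2/230 (0.9%) | 0.14 |
| 80% | 4/330 (1.2%) | 2/230 (0.9%) | 1.0 |

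As power, assuming 2% in Group 1 and 2% + excess × f in Group 2, at two-sided 5%:

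| Excess | f = 1 | 0.75 | 0.5 | 0.25 |
|---|---|---|---|---|
| 6 points | 90% | 71% | 42% | 14% |
| 4 points | 63% | 42% | 23% | 8% |

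These tables show sensitivity to f. They do not estimate it.

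**The case against.** A reader might infer that AD worsening is removed from the safety comparison altogether. The documents do not support that, for four reasons.

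- 7.1.8 counts an event when AD is only about as likely a cause as the vaccine, and its categories refer to worsening as well as new occurrence. Whether a flare is rated 'Unlikely' depends on the rater.
- The only relevant data in the protocol point away from total loss. Table III, a table of adverse reactions in the pilot trial POX-MVA-007, lists atopic dermatitis in 2 of 15 active-AD subjects (13.3%) and 0 of 15 healthy subjects. Underlying AD did not stop those events being classed as reactions.
- Unfiltered routes exist. The fifth endpoint in 9.2.2 records intensity for non-serious unsolicited events of any cause, preferred terms are compared without a filter, and serious events are compared regardless of cause. Section 9.4.4 also foresees category counts for ordinal variables of interest, so an all-causality table by grade may well be produced.
- Open-label here means only that AD status is known. Everyone receives the same vaccine, and medical history properly belongs in a causality judgement.

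All of this stands, and it limits the point to possible under-counting. It supplies no stated between-group comparison of severe unsolicited events that is independent of the relatedness rating.

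The strongest objection concerns the remedy. There is no unvaccinated AD control, Group 1 excludes atopy, and at least half of Group 2 is meant to have active AD (4.1). An all-causality excess in Group 2 would partly reflect simply having AD. That is a good reason not to replace the related-only comparison, but not a reason to show it alone.

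**Conclusion.** The point holds as a risk of bias towards no difference in one of five secondary safety endpoints. The protocol does not call this endpoint key, and the primary ELISA comparison is untouched. What the text establishes is the relatedness restriction, the raters' knowledge of AD status, and an alternative cause available in one group only. What it does not establish is how often raters would use that alternative. The size of the bias therefore cannot be derived: the 20 and 2 events, the 2% base rate, the excesses and every value of f above are assumptions. If most flares are rated 'Possible', the effect is small; if half are rated unrelated, a clear assumed difference (p = 0.001) is no longer distinguishable (p = 0.14).

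The mismatch between Grade 3 in 9.2.2 and Grade 3 or higher in 9.4.3 is a separate, definite inconsistency. That section 9 does not use SCORAD is a lesser matter, since the statistical analysis plan, not seen here, may cover it.

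**What to change.** In section 9.4.3, add a between-group comparison of Grade 3 or higher adverse events within 28 days after vaccination regardless of causality, presented alongside the related-only comparison. Tabulate skin and AD events by grade and group, also regardless of causality. Make the grade range the same in 9.2.2 and 9.4.3.

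Optionally, for Group 2 subjects with active AD, summarise the SCORAD change from screening to Visit 5 together with recorded changes in AD treatment. Section 6.6 allows limited topical therapy, so a stable score on increased treatment should not be read as absence of worsening.

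The cost is analysis text and tables. Grade, causality, SCORAD and concomitant medication are already collected. The downside is that all-causality rates will be higher in Group 2 and include background flares. The report should say that an excess there is not by itself a vaccine effect and that the two versions are to be read together.
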